#### 2.4.2. Baseline Assessment

After providing consent, all subjects will be asked to complete an online baseline survey. The baseline survey includes sociodemographic information and self-completed validated scales designed to assess the patient’s mental health outcomes. During the baseline assessment, participants will be given the option of selecting the message bank from which they want to receive text messages based on their needs (i.e., depression, anxiety, bipolar disorder, etc.). In addition to that, one clinician-rated scale, which evaluates suicidal risk, will be completed by a trained research team member in person or over the phone. The average time for completing the baseline survey is 10 min.

#### 2.4.3. Randomization and Allocation

Patients who provided consent will be enrolled in the study after completing the online baseline survey and entering a mobile phone number in the space provided. Participants will be randomly assigned to the IG or CG according to the methodology previously described.

#### 2.4.4. Follow-Up Assessment

Participants in both study arms (intervention and control) will receive a link to the follow-up self-completed online surveys through SMS and be asked to complete them at 6 weeks and 3, 6, and 12 months after enrolment in the study. The same clinician-rated scales completed at enrolment will be completed over the phone by a trained research team member. A monitoring compliance strategy will be put into practice (a reminder text message after two days and then phone calls from the research team) in order to mitigate the loss of follow-up and improve patient compliance.

#### 2.4.5. Optional Qualitative Sub-Study

A sub-sample of the study population will be invited to participate in individual interviews and focus groups. As this qualitative study does not aim to generalize findings but rather to provide depth, a purposive sampling approach will be employed to select the participants. The mental health program the participant is subscribed to, which is an indication of the primary presenting problems or diagnosis, will be considered in the selection of participants for the qualitative sub-study. In addition, sex- and gender-based representation, age groups, and marginalized groups will be considered in the sample, ensuring that a diverse group is represented in this sample. The method used to draw a heterogeneous sample will be by extracting from the database the unique study IDs and the respective mental health program, primary presenting problem/diagnosis, age, sex, gender, and ethnicity information. An Excel spreadsheet will be created for each variable, and a random sampling method will be run for each one. After drawing the sub-sample, potential participants will be invited to the sub-study via a text message. If the estimated number of participants cannot be reached after the invitations, another round of sampling and invitations will be carried out. The inclusion criteria to take part in this qualitative sub-study are having previously provided consent and being available to attend a 2 h, audio-recorded, individual interview and focus group session. The participants of the optional qualitative sub-study will be reminded of their consent, possible risks (feeling uncomfortable during the individual interviews and/or focus group while discussing their experiences with the mental health services, and risk of participant identification), and possible benefits (e.g., results may contribute to improvement in mental health services). A trained research team member will conduct the meetings in person or via Zoom Healthcare. The focus group will have a maximum of 10 participants and will last less than 1.5 h. Participants in the optional qualitative sub-study will be compensated with a gift card for their time spent in the research activities.

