Although many studies [21,22,23,24,25,26] have shown that text messaging programs can improve the mental health of a varied population, when it comes to the specific diagnoses of psychiatric conditions and different levels of care complexity, the only data available come from pilot studies limited to patients diagnosed with depression and enrolled in outpatient clinics. This proposed trial primarily aims to close this evidence gap by providing fresh data on the efficacy of a CBT-based supportive text messaging program (Text4Support), compared with usual care, in improving transdiagnostic mental health outcomes among patients accessing different degrees of formal mental health care. Secondarily, we want to look at how the intervention affects the use of health services (crisis calls, ED visits, admissions and readmissions, and LOS following inpatient hospitalization) and patient satisfaction with mental health services (overall satisfaction, retention and withdrawal rates, and patient engagement). Lastly, we will explore Text4Support implementation outcomes (reach of the intervention, acceptability, appropriateness, fidelity, and cost-effectiveness). This research protocol will be helpful for any mental health services looking to enhance patient care and health services utilization while also extending support for those who need it. The findings of this study are expected to advance our understanding of mental health innovations in a variety of clinical contexts.

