### 2.3. Sample Size Considerations

With a hypothesized difference of 20% in change scores (from baseline to the four-time points) for each of the primary outcome variables of interest (e.g., mean change score of 10 vs. 8), a population variance of 5.0 for the mean change score, a 2-sided significance level (α = 0.05), a power of 90% and an acceptable difference between the sample mean and population mean score for each scale of zero (μ − μ0 = 0), an estimated sample size of 131 participants in each arm of the study would be needed (based on the 6Sigma online script) to detect the projected mean differences in mean change scores between the intervention and control groups [29,30]. Thus, the sample size for the RCT would be 262. Given that the maximum survey completion rate for the online surveys delivered via text message is approximately 20%, in order to achieve 262 completed survey responses at each time point, we plan to enrol at least 1500 participants in the RCT. This recruitment rate is achievable since a related study in Alberta [31] currently has over 500 patients recruited within six months. The sample size for the qualitative component of the study cannot be predetermined. Data saturation is reached across data analysis, ending when no new themes and subthemes emerge. However, based on what the literature suggests [32,33], we anticipate that 25–30 participants may be sufficient for this particular mixed-method study.

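### The qualitative sub-study ignores message use when sampling and describes only a text-message invitation, so its findings may lean towards engaged users

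*Protocol article*

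**What the plan says.** Section 2.4.5 describes a purposive sample meant to be diverse. Study IDs are extracted with "mental health program, primary presenting problem/diagnosis, age, sex, gender, and ethnicity information", and a random draw is run for each variable. Whether a participant still reads the messages, rarely reads them or has stopped is not among the variables.

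The invitation is described in one sentence: "After drawing the sub-sample, potential participants will be invited to the sub-study via a text message". The remedy for low uptake follows: "If the estimated number of participants cannot be reached after the invitations, another round of sampling and invitations will be carried out". Eligibility means "having previously provided consent and being available to attend a 2 h, audio-recorded, individual interview and focus group session", and participants receive a gift card.

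Other parts of the article bear on this:

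- The Introduction gives a secondary aim of examining "patient satisfaction with mental health services (overall satisfaction, retention and withdrawal rates, and patient engagement".
- Section 2.6 says the interviews and focus groups supply experience and satisfaction data. It assigns self-reported retention and withdrawal, including texting STOP, to the satisfaction survey.
- Table 1 lists in-depth interviews as the only source for appropriateness.
- Section 2.4.4 gives the follow-up assessments a back-up: "a reminder text message after two days and then phone calls from the research team". Section 2.4.5 describes nothing similar for the sub-study invitation.

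**The concern.** The sub-study is to describe how patients experience a texting programme, and the only described way into it is to respond to a text. Willingness to engage with texts is close to the thing being studied. Someone who found the messages unhelpful and stopped reading them is informative about acceptability and appropriateness, yet nothing in the sampling ensures that such a person is included, and the contact route may make it less likely.

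Two features of the procedure add to this. Further rounds replace people who did not answer with new people who do, so repeating the procedure does not reduce the selection. Recruitment also ends at saturation (Sections 2.3 and 2.7). Among people who all answer texts, new themes may cease to appear before anyone who stopped has been heard, so saturation would not reveal the gap.

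At stake is the balance of the qualitative findings. Appropriateness is the most exposed, because Table 1 gives it no survey measure.

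**Working it through.** **What can be checked against the text.** The anticipated 25–30 participants in Section 2.3 come from literature and saturation, not from a formula, so there is no plan figure to reproduce. The check is a comparison of sections:

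| Step | Follow-up assessments (2.4.4) | Qualitative sub-study (2.4.5) |
|---|---|---|
| First contact | SMS link | text message |
| No answer | reminder text, then phone calls | new round of sampling and invitations |
| Message use considered | asked about in the satisfaction survey (2.6) | not a draw variable |

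The two procedures differ at the step that matters for people who do not answer texts.

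**Illustration of the mechanism.** Let *d* be the share of intervention invitees who have stopped, and *k* their chance of accepting a text invitation relative to the others. Their share among attenders is

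*p* = *d·k* / (*d·k* + 1 − *d*).

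Inputs, all assumptions:

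- *d* = 10% to 20%. This is loosely prompted by Section 3, which cites about 90% six-week retention in a similar programme and forecasts at least 80%. Neither is a stopping rate for this trial.
- 14 intervention attenders: half of 28, a value within 25–30, given 1:1 allocation and a draw that does not use arm.
- *k* = 1 (no channel effect) or 1/3 (no source in the article).

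| *d* | *k* | *p* | Expected among 14 | Chance of none, (1 − *p*)^14 |
|---|---|---|---|---|
| 10% | 1 | 10.0% | 1.4 | 23% |
| 20% | 1 | 20.0% | 2.8 | 4% |
| 10% | 1/3 | 0.033/0.933 = 3.6% | 0.5 | 60% |
| 20% | 1/3 | 0.067/0.867 = 7.7% | 1.1 | 33% |

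With *k* = 1/4 and *d* from 10% to 40%, *p* runs from 2.7% to 14.3%. If STOP also blocked study texts, which the article does not say, *k* and *p* would be zero.

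**What this shows.** The rows with *k* = 1 involve no bias: stoppers are then represented in proportion, but in a sample this small that means about one to three people. Any *k* below 1 lowers the number further. The direction follows from *k* < 1, which is plausible; the size depends wholly on values that the article does not give. The last column also treats 14 as fixed, whereas the plan recruits to saturation.

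**The case against.** The other side has a good deal to say, and much of it stands.

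- **The text route may not be exclusive.** Section 2.4.5 does not rule out reminders or calls, and a condensed article may omit them. This limits the point to what is described. It does not remove it, because the article spells out phone calls for the surveys and, for the sub-study, goes straight from the text to a new draw.
- **Stoppers are not under-represented in the draw.** This is correct: a random draw on the listed variables includes them in proportion. Any loss arises at the reply stage.
- **The sub-study seeks depth, not generalisation.** This is true, and binomial chances are only illustrative for such a design. But purposive sampling for depth means choosing informative cases, and Section 2.4.5 itself aims for a heterogeneous sample.
- **Stopping daily automated messages is not the same as ignoring a single invitation.** This is fair. Section 3 cites a 98% open rate for push texts, and invitees have already consented and are compensated. The reply ratio could be near 1.

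A reader might infer more than the article supports:

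- **That four in five invitees would never be heard.** Section 2.3 does say that "the maximum survey completion rate for the online surveys delivered via text message is approximately 20" per cent, and at that rate 25–30 attenders would need 25/0.20 = 125 to 30/0.20 = 150 invitations. But the figure is for survey completion. At reply rates of 40–60% the need is about 42 to 75 invitations.
- **That the reasons for stopping are a stated objective that will be missed.** The Introduction names rates of retention and withdrawal, and Section 2.6 assigns these to the survey.
- **That the satisfaction survey shares the same defect.** It goes out by SMS link, but Section 2.4.4 gives it phone follow-up.

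**Conclusion.** The concern holds in a limited form. As described, the sub-study takes no account of message use, invites by text, and replaces people who do not answer. That plausibly tilts the qualitative findings on experience, acceptability and appropriateness towards people who still engage with texts. It rests on one assumption that the article neither states nor excludes: that people who stopped or ignore the messages are less likely to answer a text invitation.

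The size cannot be derived. The illustrative chances of hearing no stopper run from 4% to 60%, and most of that spread comes from assumed inputs. They should not be read as an estimate, nor as showing that the findings will be favourable.

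The point does not reach the clinical outcomes, service utilisation, the quantitative satisfaction survey or randomisation. It is a worthwhile improvement to a stated method.

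**What to change.** In Section 2.4.5:

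1. Add message use as a purposive sampling variable for intervention participants: still reading, rarely reading, or stopped. Take it from the satisfaction survey and any STOP record. Make survey non-response its own category, since reading status will be missing for many of the people of most interest. Aim to include some intervention participants who stopped or rarely read.
2. Follow an unanswered text invitation with a phone call, for example on the reminder or C-SSRS call already planned in Section 2.4.4. Because Section 2.1 describes the trial as rater-blinded, an invitation on the C-SSRS call should come after the rating and should not touch on arm or message use.
3. Report invited versus attending participants by message use, so that readers can see any remaining selection.

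The cost is a short wording change, a few extra calls by staff who already phone participants, and slightly slower sub-study recruitment. The trial's sample size and its quantitative analyses do not change.

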### 2.5. Proposed Interventions

The intervention to be tested in this trial is the Text4Support program, which will be compared with a control condition. A day after enrolment, the participants randomized to the IG (Text4Support) will start receiving daily unidirectional (no-reply), CBT-based, diagnostic-specific supportive text messages for 6 months, as an add-on program to their usual care, with a subsequent observation period of 6 months, totaling 12 months of follow-up. Text4Support is powered by ResilienceNHope [34], an online application offered by the Global Psychological eHealth Foundation [35]. In action, Text4Support provides general content indicated regardless of the symptomatology presented, including messages of self-care, social support, hope, affirmation, and recovery (Figure 2a), as well as diagnostic-specific content focused on managing symptoms related to the diagnosis, such as the examples shown in Figure 2b,c. It is possible to observe the principles of the CBT cognitive triangle (thoughts, feelings, and actions) in the text messages shown, which is a key component of the program’s therapeutic effect. The text messages always encourage the recipients to consider their thoughts and feelings, and they suggest actions to take. The text message bank includes 180 messages per category (i.e., stress, mood disorders, anxiety disorders, depression, schizophrenia and other psychotic disorders, substance use disorders, adjustment disorders, and personality disorders). The messages were originally developed in Canadian English, and while the online application allows for translation into other languages such as French, Punjabi, Arabic, Ukrainian, Russian, and simplified Chinese, the proposed program will only be delivered in English. The program targets individuals who are receiving any type of assessment and/or treatment from mental health and addiction services. The subscribers can choose the bank of messages they want to receive based on their primary mental health concerns. The possibility of covering a wide range of mental health conditions, from the most to the least frequent and from mild to critical disorders, means that it can be used to augment mental health support for patients receiving various levels of mental health care in accordance with the project’s goals.

The control condition comprises the standard care offered by each program/unit participating in this study (i.e., follow-up appointments or offering of community clinic/program treatment) and a single text message with the link to the e-mental health resources available on the NS Health MHAP website [36], following 12 months of the observational period. Currently, the NS Health MHAP website offers 22 freely accessible, evidence-based e-mental health tools covering a wide range of psychiatric conditions (i.e., substance abuse disorders, gambling, depression, anxiety, grief, bipolar disorders, eating disorders, obsessive–compulsive disorder, post-traumatic stress disorder, schizophrenia, and psychosis, among others), group ages (children, youth, adult, and seniors) and group identities (Black/African Nova Scotians, 2SLGBTQIA+, Canadian Forces, RCMP, caregivers and families, First Nations/Indigenous people, and first responders).

### 2.6. Outcome Measures

The intervention effectiveness will be determined by evaluating the differences between the intervention and control group from baseline and the subsequent time points (6 weeks and 3, 6, and 12 months) for patient clinical outcomes and the differences between groups for health service utilization at 12 months, and the implementation success will be measured through quantitative and qualitative patient satisfaction data and implementation indicators, as follows:Clinical outcomes: The primary clinical outcome will be the differences in mean change in patient recovery and quality of life, assessed through the Recovery Assessment Scale (RAS) [37] and the World Health Organization Five Well-Being Index (WHO-5) [38]. Secondary clinical outcomes will include the differences between the intervention and control groups in prevalence changes for moderate-to-high depression (likely major depressive disorder), moderate-to-high anxiety (likely generalized anxiety disorder), and low resilience from the baseline to these time points, assessed through the Patient Health Questionnaire-9 (PHQ-9) [39], Generalized Anxiety Disorder-7 scale [40], and the Brief Resilience Scale (BRS) [41]. The mean score differences between groups from the baseline to determine time points will also be assessed using the Adverse Childhood questionnaire (ACE questionnaire) [42], and the Brief Substance Use Craving Scale (BSCS) [43], which will be used to assess childhood trauma and substance craving, as well as the clinician-rated Columbia-Suicide Severity Rating Scale (C-SSRS) [44], which will be used to assess suicide risk.Health service utilization outcomes: Health service utilization data will be extracted by the registration, reporting, and analytics, mental health and addiction team from the multiple health information systems utilized across NS Health and provided to the research team through reports. The differences in health service utilization data (mobile crisis visits, number of ED presentations, number of admissions in the last 12 months, length of stay, and the number of hospital readmissions) will be evaluated for participants in both groups. The differences between groups will be evaluated at 12 months.Patient experience and satisfaction outcomes: Patient satisfaction and patient experience with the e-mental health interventions (Text4Support and other e-mental health programs offered freely through NSH Authority) will be evaluated using both quantitative and qualitative data. Overall satisfaction will be assessed at each of the four time points (6 weeks and 3, 6, and 12 months) using a self-designed scale. Self-reported retention and withdrawal will both be assessed through the satisfaction survey, which addresses questions about the frequency of reading messages, the frequency of returning to messages stored in their phones, and actions taken by the participants after reading the text messages or freely available e-mental health resources (i.e., text “STOP”, clicking on links, searching for more information) up to 12 months after enrolment. Patient experience and satisfaction qualitative data will be collected through individual interviews and focus groups.Implementation Outcomes: Implementation outcomes are indicators of implementation efforts and are distinct from service or clinical outcomes [45]. For the intervention arm, we will include the reach of the interventions, acceptability, appropriateness, fidelity, and cost-effectiveness, evaluated at each of the four time points [28]. These implementation indicators will not be collected from the e-mental health or website visits in the control arm because they are not tied to the patient’s study ID and cannot be linked to the other measures.

Quantitative clinical and health services utilization outcome measures and time points are detailed in Table 1.

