### 2.7. Data Analysis

Quantitative data will be analyzed in concordance with the CONSORT guidelines [46]. The baseline demographic and clinical characteristics of the two groups will be analyzed using Chi-squared, Fisher’s Exact, and Student’s *t*-tests. The primary (clinical mental health outcomes) and secondary outcome (health services utilization) measures will be analyzed using descriptive and inferential statistical analysis, and Bonferroni correction will be used when necessary. The scores at each time point on standardized rating scales for clinical variables (PHQ-9, GAD-7, WHO Five Well-Being Index, BRS, RAS, ACE, C-SSRS, and BSCS) will each be compared between the intervention and control groups using an analysis of covariance (ANCOVA) with the treatment condition as the independent variable, the baseline scores on clinical variables as the covariate, and the scores at each time point on standardized rating scales as the dependent variable. In each case, checks would be conducted to ensure the reliable measurement of the covariate and no violation of the statistical assumptions of normality, linearity, homogeneity of variance, and homogeneity of regression slopes. Multiple imputations will be our baseline approach to addressing missing data, although analysis of missingness patterns must be performed to inform our specific assumptions, implementation, and interpretation during missing data analysis. Sensitivity analyses will also be conducted with respect to the imputation approach, including a comparison with the last observation carried forward, mean/median imputation, best case, worst case, and complete case analyses. The reasons for discrepancies between approaches will be analyzed and discussed in the study manuscript. We will also compare the prevalence scores for the clinical variables of interest using Chi-square/Fisher’s exact tests. To explore the impact of select demographic and clinical variables on the clinical variables of interest, we will perform a two-way between-groups = analysis of variance. Characteristics of individuals/clusters will be summarized by exposure status to allow the consideration of selection biases and lack of balance [47]. In terms of the number of multiply imputed datasets to be analyzed, we will begin with 100 datasets. A sensitivity analysis will subsequently increase this number to ascertain the stability of model estimates in relation to the number of multiply imputed datasets.

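### Two primary scales at four time points, none of them primary, are sized as one test at 0.05, and the Bonferroni clause fixes neither a family nor a divisor

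*Protocol article*

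**What the plan says.** **Outcomes.** Section 2.6 (Outcome Measures) defines the primary outcome: "The primary clinical outcome will be the differences in mean change in patient recovery and quality of life". The two instruments it names for this are RAS and WHO-5. The same section compares the arms at "the subsequent time points (6 weeks and 3, 6, and 12 months) for patient clinical outcomes". It names no time point as primary. It lists the depression, anxiety and resilience outcomes (PHQ-9, GAD-7, BRS) as secondary.

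**Sample size.** Section 2.3 sizes each primary variable, for change from baseline to the four time points, with "a 2-sided significance level (α = 0.05), a power of 90"%. The example effect is "e.g., mean change score of 10 vs. 8", the printed population variance is 5.0, and the result is 131 per arm. At least 1500 are to be enrolled because survey completion is put at a maximum of about 20%.

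**Analysis.** Section 2.7 (Data Analysis) plans an ANCOVA for each scale with the score at each time point as the dependent variable and the baseline score as covariate. On multiplicity it says "Bonferroni correction will be used when necessary". It also says "The primary (clinical mental health outcomes) and secondary outcome (health services utilization) measures will be analyzed", which applies the word primary to clinical outcomes as a whole.

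**The concern.** Two scales at four times, each with its own ANCOVA, make eight primary tests. The plan does not say which of them decides whether the trial is positive, or whether all must succeed or any one will do. The sizing spends the whole 0.05 on one test. The correction clause has no stated family, divisor or trigger.

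Two outcomes are therefore possible:

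- If no correction is made, any one of eight tests can be presented as a positive primary result, and the overall false-positive rate is well above 5%.
- If a correction is made, the trial has been sized at a significance level it will not use.

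Because the clause is conditional, the choice between the two could be made after the results are known. The broader use of primary in section 2.7 also leaves it unclear whether PHQ-9, GAD-7 and BRS belong to the primary family.

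**Working it through.** **Inputs from the protocol article.** Difference in mean change 10 − 8 = 2; two-sided alpha 0.05; power 90%; printed variance 5.0; 131 per arm; 1:1 allocation; enrolment of at least 1500; completion about 20% (section 2.3). Two primary scales, four time points (section 2.6).

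**Step 1: reproduce 131 per arm.** For two means, n per arm = 2σ²(z₀.₉₇₅ + z₀.₉₀)²/δ², with (1.960 + 1.282)² = 10.507 and δ² = 4.

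- Variance 5.0 as printed: 2 × 5 × 10.507 / 4 = 26.3, so 27 per arm.
- 5.0 read as the SD (variance 25): 2 × 25 × 10.507 / 4 = 131.3, which matches the stated 131.

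So 131 follows only if 5.0 is the SD, giving a standardised effect of 2/5 = 0.40. It also uses the undivided 0.05.

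**Step 2: false positives without correction.** Eight independent tests at 0.05 give 1 − 0.95⁸ = 0.337. The tests will be correlated, but the document gives no correlations, so a range was simulated (eight normal test statistics, two-sided 0.05):

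| Assumed correlation | All pairs equal | Scale × time product structure |
|---|---|---|
| 0.5 | 25.0% | 26.8% |
| 0.6 | 22.1% | 24.1% |
| 0.7 | 19.0% | 20.9% |

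In the product structure, pairs that differ in both scale and time have the square of the listed correlation (0.25 to 0.49). Across both structures the range is about 19–27%. This step does not depend on the variance.

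**Step 3: power with correction, if the SD is 5.** Two-sample t-test, noncentrality 2/(5√(2/n)), which is 3.24 at n = 131 and 3.46 at n = 150. The 150 is 1500 × 0.20 / 2.

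| Alpha per test | 131 per arm | 150 per arm |
|---|---|---|
| 0.05 | 89.7% | 93.2% |
| 0.05/2 = 0.025 | 83.7% | 88.7% |
| 0.05/8 = 0.00625 | 68.4% | 76.1% |

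By the Step 1 formula with the new alpha, 90% power would need 156 per arm at 0.025 and 202 per arm at 0.00625.

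**Step 4: power with correction, if the variance is 5.0 as printed.** The same formula gives 32 per arm at 0.025 and 41 per arm at 0.00625. At 131 per arm, power is above 99.9% at either level.

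**Step 5: effect of ANCOVA.** Assume that 5 is the SD of the change score, that baseline and follow-up variances are equal, and that their correlation is ρ. Baseline adjustment then multiplies the change-score variance by (1 + ρ)/2. The document does not give ρ. At 0.05/8:

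| ρ | Effective SD | 131 per arm | 150 per arm |
|---|---|---|---|
| 0.3 | 4.03 | 89% | 94% |
| 0.5 | 4.33 | 84% | 89% |
| 0.7 | 4.61 | 77% | 84% |

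**The case against.** A reader might infer that the trial simply lacks its stated 90% power. The documents do not support that without conditions.

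- **Variance or SD.** The loss appears only if 5.0 is the SD. On the printed variance, 131 per arm is ample even at 0.05/8. This objection stands, and it makes the power claim conditional.
- **Small loss under a narrow family.** With one time point, two scales and 150 completers per arm, power is 89%. Holm is never less powerful than the plain 0.05/2 behind that figure. This also stands. However, 150 relies on a completion rate that section 2.3 calls a maximum, although 1500 is a minimum enrolment.
- **ANCOVA and imputation.** The planned adjustment can recover much of the loss (Step 5), and multiple imputation means the information may differ from completers only. This stands as a caveat on the 68% and 76%, but neither affects the false-positive rate.
- **Contradiction.** It is tempting to say that the outcome definition, the sizing and the correction clause cannot all hold. A conditional clause is vague, not contradictory. The labels in section 2.7 can be read as naming domains, clinical against service use, with section 2.6 ranking scales inside the clinical domain. The wording still has to be aligned.
- **Larger families.** One might correct over all eight scales at four times. Table 1 collects ACE at baseline only, and section 2.6 makes only RAS and WHO-5 primary, so a 32-test family has no support.
- **Left to the analysis plan.** Details of a correction often are. What remains is that the article itself fixes the sizing alpha for a single test and sets out eight primary tests without ranking them. A later document cannot put that right while these sections stand as written.

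**Conclusion.** The concern holds in conditional form. The protocol article sets up eight primary tests with no primary time point, sizes for one test at 0.05, and leaves the correction open.

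The false-positive consequence is firm in direction: without correction, 34% under independence and about 19–27% under assumed correlations of 0.5–0.7, against a nominal 5%.

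The power consequence depends on two things the document leaves unsettled: whether 5.0 is an SD, as 131 implies, and how many tests the correction covers. If it is an SD, unadjusted per-test power is 84% (two tests) or 68% (eight) at 131 per arm, and 89% or 76% at 150. ANCOVA may raise these. If it is a variance, power is not threatened.

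The point decides what counts as a positive trial, so it should be settled before outcome data are seen.

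**What to change.** Before outcome data are seen:

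1. In section 2.6, name one primary time point. The choice is the sponsor's; 6 months, when message delivery ends, is one candidate. Make the other time points and all other scales secondary.
2. In section 2.7, replace the conditional clause with Bonferroni-Holm over RAS and WHO-5 at family-wise two-sided 0.05. Use the word primary for those two scales only, as section 2.6 does.
3. In section 2.3, state first whether 5.0 is a variance or an SD, then restate power at the corrected alpha. If it is an SD, this is about 84% per scale at 131 per arm or 89% at 150, before any gain from baseline adjustment.
4. If the sponsor prefers to keep all eight tests primary, state power at 0.05/8: 68% at 131 per arm or 76% at 150, unadjusted. Any credit for ANCOVA should come with a stated and justified baseline correlation.

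**Cost.** Changes of wording in three sections and no extra patients. The other time points lose primary status, and the stated power may be slightly lower than 90%.
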